#### Planned methods of statistical analysis for safety-related aims

The safety analysis will be performed in the safety set. Treatment-emergent AEs (events with an onset date on or after the first study drug administration until 70 days following the last study drug administration) will be summarised by treatment group using descriptive statistics. SAEs with onset after informed consent but before the first study drug administration will be considered as pretreatment SAEs and reported separately.

AEs will be tabulated by system organ class and preferred term whereby the most current implemented MedDRA dictionary will be used. In addition, summaries by severity and relationship to study drug will be done. Certain AEs, such as serious or severe, leading to premature withdrawal, will be listed and described in detail. AEs of special interest for treatments will be defined in the statistical analysis plan and analysed separately. In addition to the descriptive statistics provided, Fisher’s exact test will be used for comparisons between treatment groups.

#### Genetic analysis

SNPs genotypes will be determined by real-time PCR amplification using Taqman probes and following standard procedures. Duplicate genotypes of 10% of the samples, concordance (all p>0.05) with the Hardy–Weinberg equilibrium and with SNP frequencies in the HapMap European collection will be used for quality control.

Comparison of the proportion of subjects achieving the primary efficacy outcome between genotypes will be carried out using a χ^2^ test or Fisher’s exact test, when required. Dominant, recessive and additive models of effects will be considered for each SNP. P values will be adjusted using the Bonferroni method. Each study arm will be analysed separately.

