**Methods and analysis:**

The Combination THerapy with mEthotrexate and adalImumAb for uveitis (CoTHEIA) study is a phase III, multicentre, prospective, randomised, single-blinded with masked outcome assessment, parallel three arms with 1:1:1 allocation, active-controlled, superiority study design, comparing the efficacy, safety and cost-effectiveness of methotrexate, adalimumab or their combination in non-infectious non-anterior uveitis. We aim to recruit 192 subjects. The duration of the treatment and follow-up will last up to 52 weeks, plus 70 days follow-up with no treatment. The complete and maintained resolution of the ocular inflammation will be assessed by masked evaluators (primary outcome). In addition to other secondary measurements of efficacy (quality of life, visual acuity and costs) and safety, we will identify subjects’ subgroups with different treatment responses by developing prediction models based on machine learning techniques using genetic and proteomic biomarkers.

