*Pharmacogenetic and proteomic-related objectives* include identifying groups of subjects more likely to respond to the different treatment strategies, using genetic and proteomic biomarkers. For the former, subjects will be genotyped for known and validated genetics single nucleotide polymorphisms (SNPs) associated with a MTX^54^ and ADA^55^ response in different IMIDs. For the latter, a Discovery (shotgun proteomic analysis), Verification (targeted proteomics using multiple reaction monitoring (MRM) test) and Validation (antibody-based microarrays absolute quantification tests) phases will be carried out, following optimised protocols and procedures.^56–61^

Finally, a *Biobank substudy-related objective* will be carried out with the aim of boosting the translational research in the field of NIUs, by creating a collection of blood-derived samples (serum, plasma, total blood RNA and DNA) from the participant subjects in order to advance in the identification and validation of biomarkers associated with treatment response or deepen in the pathophysiology of these conditions.

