#### Patient subgroup identification

Based on baseline visits patient’s characteristics (demographic, disease and clinical-related variables), those genotypes significantly associated with the primary efficacy outcome, and the previously identified serum proteins in the verification phase, prediction models for MTX, ADA and Combination therapy response will be developed using a machine learning method (Random Forests^67^). Models’ performance will be assessed with the area under the receiver operating characteristic curve, and calibration curves. Models using only clinical data, only biomarkers data and the combination of both will be developed, to assess the contribution of biomarkers to the models’ predictive ability. Due to the modest sample size we plan to recruit, we will not divide our sample in training, validation and test data sets. All subjects will be considered as part of the training data set, and a 10-fold cross-validation will be carried out to internally validate our models.

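### Genotype is tested against response only within each arm, so the stated analysis cannot tell a SNP that predicts differential drug response from one that is merely prognostic

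*Protocol article*

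**What the plan says.** The Objectives section gives the pharmacogenetic and proteomic aim as "identifying groups of subjects more likely to respond to the different treatment strategies, using genetic and proteomic biomarkers". The abstract puts it as a search for subgroups: "we will identify subjects’ subgroups with different treatment responses by developing prediction models based on machine learning techniques".

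The Genetic analysis section fixes the method: "Comparison of the proportion of subjects achieving the primary efficacy outcome between genotypes will be carried out using a χ^2^ test or Fisher’s exact test". It adds "Dominant, recessive and additive models of effects will be considered for each SNP", calls for Bonferroni adjustment, and ends with the rule "Each study arm will be analysed separately".

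Under Patient subgroup identification, the genotypes that pass ("those genotypes significantly associated with the primary efficacy outcome") join clinical variables and proteins, and "prediction models for MTX, ADA and Combination therapy response will be developed" by random forests. These models are judged by area under the ROC curve and calibration.

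The only interaction named in the article is time by arm, for EQ-5D in Table 4. None involves genotype.

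**The concern.** Whether a genotype changes the response to one strategy more than to another is a between-arm question. Three separate within-arm tests do not answer it. With at most 64 subjects per arm each test has low power, so a SNP with the same effect everywhere will commonly reach significance in one or two arms and miss in the rest. That pattern resembles a treatment-specific effect and is no evidence of one.

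Nothing downstream repairs this. AUC and calibration show how well a model predicts within a treatment, not whether a marker's effect differs between treatments. A prognostic SNP could therefore pass every stated step and appear in one drug's model only. At stake is the interpretation of the biomarker objective; the primary efficacy analysis is untouched.

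**Working it through.** **Inputs from the article.** Response is 43% on either monotherapy and 43 + 23 = 66% on the combination. The article needs 54 per arm, or 64 after 15% losses.

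**The article's own figure.** A two-sided 0.05 test with 80% power, combination against pooled monotherapies (1:2), has mean rate (0.66 + 2×0.43)/3 = 0.507.

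n = [1.960·√(1.5×0.507×0.493) + 0.842·√(0.66×0.34 + 0.43×0.57/2)]² / 0.23² = 54.4

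This agrees with the stated 54. Then 54/0.85 = 63.5, rounded up to 64. No power is stated for the genetic work.

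**Assumptions, because the article gives no figures.** Carriers 40%, so 26 carriers and 38 non-carriers per arm. A purely prognostic SNP with the same risk difference d in every arm: non-carriers respond at the arm rate + 0.4d, carriers at the arm rate − 0.6d. Effects of 10, 15 and 25 points (odds ratios about 1.5, 1.9 and 3). Bonferroni for 10 or 30 tests. All 64 per arm analysed.

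**Formulas.** Power in one arm = Φ[(d − z·SE₀)/SE₁], with SE₀ pooled and SE₁ unpooled. With arm powers p₁, p₂, p₃:
- P(none) = Π(1 − pᵢ)
- P(all) = Πpᵢ
- P(some but not all) = 1 − P(none) − P(all)
- Arm-specific given flagged = P(some but not all) / (1 − P(none))

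**Worked case: 25 points, 10 tests (alpha 0.005, z = 2.807).**
- Combination, 76% v 51%: (0.25 − 2.807×0.1207)/0.1200 = −0.74, power 0.230.
- Each monotherapy, 53% v 28%: (0.25 − 2.807×0.1259)/0.1196 = −0.87, power 0.193.
- P(none) = 0.770×0.807² = 0.501; P(all) = 0.230×0.193² = 0.009.
- P(some but not all) = 1 − 0.501 − 0.009 = 0.49.
- Given flagged: 0.490/0.499 = 98%.

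| Effect | Tests | Power (combination / each monotherapy) | Some but not all arms | Arm-specific, given flagged |
|---|---|---|---|---|
| 10 points | 10 | 0.025 / 0.021 | 6.5% | >99.9% |
| 15 points | 10 | 0.060 / 0.049 | 15% | 99.9% |
| 25 points | 10 | 0.23 / 0.19 | 49% | 98.3% |
| 10 points | 30 | 0.011 / 0.009 | 3% | >99.9% |
| 15 points | 30 | 0.029 / 0.023 | 7% | >99.9% |
| 25 points | 30 | 0.14 / 0.11 | 32% | 99.5% |

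**Cross-check by simulation** (40,000 trials per scenario, equal odds ratio in all arms, 50% carriers, 64 per arm, 30 tests). Some but not all arms: 10% at OR 2 and 35% at OR 3, and over 99% arm-specific once flagged. With 54 per arm the first two figures are 7% and 27%. With 20% carriers and 64 per arm they are 4% and 15%.

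**What a between-arm test does** (2-df test of equal log odds ratios, 64 per arm, 50% carriers). A purely prognostic SNP is flagged as treatment-specific in about 3.5–4.5% of trials at 0.05 and under 0.1% at 0.05/30. For a SNP acting in one monotherapy arm only, power at 0.05 is about 14% (OR 2), 30% (OR 3) and 57% (OR 5). At 0.05/30 it is about 1%, 3% and 13%.

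**The case against.** **The harmful inference is not written down.** The article nowhere says that significance in one arm and not another will be read as a reason to choose a drug. Genotyping is limited to SNPs already linked to methotrexate or adalimumab response in other diseases, and a prognostic predictor is legitimate in a model of response to one treatment. This stands: within-arm testing is a coherent screen for arm-specific prediction. It does not meet the differential aim stated in the abstract and the Objectives.

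**The unseen analysis plan may add an interaction.** It may. But the article does more than stay silent: it prescribes separate-arm analysis, so a between-arm test would have to be added to that rule.

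**The rate of misleading patterns may be small.** This stands in part. A reader might infer that a prognostic SNP will usually be misread, citing the 75% obtained for a 25-point effect at an unadjusted 0.05. The article states a Bonferroni adjustment and supports no such effect size, and with weak effects and many tests the figure falls to a few percent. The share among flagged SNPs is the steadier number.

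**Wasted data.** A reader might also infer that the plan discards a clean comparison of about 128 subjects given a drug against an arm without it. The design does not offer one: the arm without methotrexate receives adalimumab, and the reverse. With genotype by methotrexate as the only interaction, a SNP acting only through adalimumab (OR 3) is flagged as a methotrexate marker in about 14% of trials at 0.05.

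**Interaction tests are weak here.** True. That argues for exploratory labelling, not for a test of a different question.

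**Conclusion.** The point holds as a mismatch between aim and method: the stated genetic analysis cannot distinguish predictive from prognostic SNPs. The chance that a given prognostic SNP shows an arm-specific pattern runs from about 3% to 49% over effects of 10 to 25 points and 10 to 30 tests. It rests on assumed effect size, carrier share and number of tests, so no single rate should be quoted. Over that range, a prognostic SNP flagged in any arm looks arm-specific about 98% of the time or more. A heavier correction makes flags rarer but no more informative about differences between arms. The matter is moderate: it should be corrected, but it concerns a secondary biomarker objective.

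**What to change.** For each SNP, fit one logistic model in all randomised subjects with genotype, three-level treatment arm (two indicators), uveitis location and genotype by arm (2 df). Each genetic coding used counts towards the Bonferroni family.

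- Do not enter methotrexate, adalimumab and a separate term for both. No arm receives neither drug, so methotrexate + adalimumab − both = 1 in every arm, and with an intercept the four treatment columns have rank 3.
- Any drug-specific contrast must include genotype by methotrexate and genotype by adalimumab together. Genotype by methotrexate is then identified by combination against adalimumab alone (64 v 64), and the reading assumes that the two drugs' SNP effects are additive on the log-odds scale. State that assumption.
- Report the common genotype effect as prognostic. Keep per-arm results as description, or as screening for the arm-specific prediction models.
- Claim differential response only on the Bonferroni-adjusted interaction, and label it exploratory.

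The cost is analysis wording only, with no new data. The downside is low power: about 30% at 0.05 for a SNP with an odds ratio of 3 in one arm only, and a few percent after heavy Bonferroni. Few SNPs will be claimed as treatment-specific.

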#### Proteomic analyses

Discovery phase: Shotgun proteomic analysis^56–58^ will be performed on serum samples from a representative group of subjects from each study arm with extreme responses (n=20): those achieving the *primary efficacy outcome* and those not being able to achieve a good clinical response by week 16.

Verification phase: targeted proteomics will be used for verification of protein markers with predictive potential in a randomly selected larger samples set (n=80). After MRM tests, relative quantification methods of the proteins will be designed.^59^

Validation phase: best candidates from the previous phase will be validated using absolute quantification tests (antibody-based microarrays) in the whole set of subjects.^60 61^

#### Patient subgroup identification

Based on baseline visits patient’s characteristics (demographic, disease and clinical-related variables), those genotypes significantly associated with the primary efficacy outcome, and the previously identified serum proteins in the verification phase, prediction models for MTX, ADA and Combination therapy response will be developed using a machine learning method (Random Forests^67^). Models’ performance will be assessed with the area under the receiver operating characteristic curve, and calibration curves. Models using only clinical data, only biomarkers data and the combination of both will be developed, to assess the contribution of biomarkers to the models’ predictive ability. Due to the modest sample size we plan to recruit, we will not divide our sample in training, validation and test data sets. All subjects will be considered as part of the training data set, and a 10-fold cross-validation will be carried out to internally validate our models.

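### Proteins are selected on the outcomes of subjects who also serve in the validation phase and the cross-validation, so biomarker AUCs and their apparent gain over clinical models are liable to be optimistic

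*Protocol article*

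**What the plan says.** Under Proteomic analyses (Protocol article), discovery uses serum from trial subjects picked for extreme outcomes: those who met the primary outcome and those without a good response by week 16 (n=20; whether per arm or in total is unclear). Verification is done "in a randomly selected larger samples set (n=80"). The text does not say that these subjects are distinct from the discovery subjects. Validation is by absolute quantification ("antibody-based microarrays) in the whole set of subjects".

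Under Genetic analysis, SNPs are tested against the primary outcome in each arm separately, with Bonferroni adjustment.

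Under Patient subgroup identification, the models for MTX, ADA and combination response use baseline characteristics plus "those genotypes significantly associated with the primary efficacy outcome, and the previously identified serum proteins in the verification phase". On data use, the article says "we will not divide our sample in training, validation and test data sets" and "All subjects will be considered as part of the training data set", and that "a 10-fold cross-validation will be carried out to internally validate our models". Performance is measured by the "area under the receiver operating characteristic curve, and calibration curves". Clinical-only, biomarker-only and combined models are built "to assess the contribution of biomarkers to the models’ predictive ability".

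**The concern.** Cross-validation gives a fair estimate only if everything learned from the outcomes is relearned without the held-out fold. Here the protein list is settled before folding, from outcomes of subjects who later sit in the held-out folds. Random Forest fitting is cross-validated, but on the text as it stands the choice of predictors is not. A protein that separated responders by chance in the discovery or verification subjects will do so again when those subjects are scored.

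The validation phase has the same weakness, because the whole set contains the discovery and verification subjects.

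At stake is the question the three model types are meant to answer, namely what biomarkers add. Only the biomarkers pass through an outcome-based filter, so any optimism falls on their side.

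**Working it through.** **Inputs from the article.** The plan's own figure reproduces: 54 / (1 − 0.15) = 63.5, rounded up to 64 per arm, and 3 × 64 = 192. Assumed response is 43% on monotherapy and 43 + 23 = 66% on the combination, or (43 + 43 + 66)/3 ≈ 51% with arms pooled. Discovery is 20, or 3 × 20 = 60 if per arm. Verification is 80, which must be a total because an arm has only 64; that is about 80/3 ≈ 27 per arm. The article states no AUC and no expected optimism.

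**Inputs assumed.** The numbers of proteins screened, carried forward and kept are not given. The main simulation assumes 300 (or 100) screened, 20 carried to verification and 5 kept.

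**Can selection be nested?** Shotgun data are planned only for the discovery subjects, so that step cannot be rerun in each training fold. The SNP filter, and a final choice among proteins measured in everyone, can be.

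**Null simulation.** No marker or clinical variable is related to outcome, so the true AUC is 0.50. Discovery ranks proteins in equal numbers of responders and non-responders, verification re-ranks them in a random subset, and the top 5 enter a Random Forest with 10-fold cross-validation. There were 60 runs per one-arm scenario and 20 for the pooled one; standard errors are about 0.01.

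| Scenario | Proteins, selected before folding | Proteins, selected inside folds | Clinical only | Clinical + pre-selected proteins | Pre-selected proteins, new subjects |
|---|---|---|---|---|---|
| Arm of 64, 43% response, 300 candidates, discovery 20 | 0.668 | 0.502 | 0.486 | 0.647 | 0.495 |
| Same, 66% response | 0.665 | 0.524 | 0.506 | 0.648 | 0.491 |
| Arm of 64, 43% response, 100 candidates, discovery 20 | 0.628 | 0.485 | 0.485 | 0.610 | 0.497 |
| Arm of 64, 43% response, 300 candidates, discovery 6 (about 20 in total) | 0.592 | 0.492 | 0.486 | 0.576 | 0.502 |
| Pooled 192, 300 candidates, discovery 20 in total | 0.547 | 0.507 | 0.488 | 0.539 | 0.500 |

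The inside-folds column reruns discovery too. It is a benchmark that the trial cannot fully attain.

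**Apparent biomarker gain from noise** (clinical plus proteins, minus clinical only): 0.647 − 0.486 = 0.161 at most in one arm, 0.576 − 0.486 = 0.090 at least in one arm, and 0.539 − 0.488 = 0.051 pooled.

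**Sensitivity to the assumptions.**
- With 300 screened, 30 carried, 10 kept and a correlation of 0.8 between assays, AUC was 0.59 to 0.64 in one arm, and 0.54 to 0.55 with all 192 subjects and discovery of 20 per arm.
- With 300 screened, 2 to 5 kept and a simple linear classifier, it was 0.61 to 0.70 in one arm and 0.58 pooled.
- With only 1 to 2 proteins passing a p<0.05 filter and all 192 subjects used, it was 0.50, so no visible optimism.

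**Genotype route.** If Bonferroni covers all SNPs and genetic models within an arm, the chance of any false selection is at most about 5% per arm, and 1 − 0.95³ = 14% over three arms.

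**Untouched subjects.** If the two samples do not overlap, 192 − 20 − 80 = 92 remain, or 192 − 60 − 80 = 52 if discovery is 20 per arm. That is about 31 or 17 per arm. The Hanley–McNeil variance is [A(1−A) + (n₁−1)(Q₁−A²) + (n₀−1)(Q₂−A²)]/(n₁n₀), with Q₁ = A/(2−A) and Q₂ = 2A²/(1+A). At an assumed A = 0.7, Q₁ = 0.538 and Q₂ = 0.576. For n = 31 at 43% response, n₁ = 13.3 and n₀ = 17.7, giving SE ≈ 0.098 and a 95% half-width of about 0.19. For n = 17 it is about 0.26, and for the full 64 about 0.13. Response at 66% gives nearly the same values.

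**The case against.** A reader might infer that the article says selection stays outside the folds. It does not; it is silent, and a condensed article may leave that to the full protocol or SAP. This stands for the genotype filter and for any last choice among proteins measured in everyone. It does not rescue the discovery step, which no SAP wording could nest given where the shotgun data exist. Nor does it remove the overlap of subjects, which the text makes explicit.

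A reader might also put genotypes and proteins on the same footing. The candidate SNPs come from outside evidence (Objectives and outcome variables) and are Bonferroni-adjusted, so that route leaks less.

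It can be said that validation here names an assay stage (shotgun, then targeted, then antibody microarray) and that only internal validation of the models is claimed. That is fair as to wording. An internal estimate is still meant to be roughly unbiased, and the planned clinical-versus-biomarker comparison relies on it.

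The article declines to split the sample because it is modest, and the half-widths above bear that out: 17 or 31 subjects per arm cannot usefully compare two models. Those subjects also lack the extreme responders taken for discovery. They should not be treated as a proper validation set.

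Finally, this is a biomarker objective. The Mantel–Haenszel primary analysis and the safety conclusions do not depend on it.

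**Conclusion.** The concern holds for the protein markers. The overlap between selection and evaluation subjects is written into the plan. That selection is not repeated within folds is an inference, strong for proteins and weaker for genotypes. The biomarker AUCs, and the gain over clinical-only models, are therefore liable to be too high.

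Under no true signal and the assumed protein counts, the AUC is about 0.59 to 0.70 in one-arm models and 0.54 to 0.58 pooled, against 0.50. The one-arm figures are the more relevant, since the article names models for each treatment. The stronger claim, that the AUCs will be materially inflated whatever is done, is not supported: the article gives neither the number of proteins screened nor the number kept, and the optimism can vanish when very few survive and arms are pooled. The matter should be corrected, but it does not threaten the trial's main conclusions.

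**What to change.** 1. Repeat every repeatable outcome-based selection step inside each of the 10 folds: the SNP filter, and the final choice among proteins measured in all subjects.
2. Draw the verification sample from subjects not used in discovery.
3. Describe whole-set AUCs and the biomarker-versus-clinical comparison as development-only and optimistic, not as validated. This label is needed even after step 1, because the discovery step remains outside the folds.
4. Report performance in subjects used in neither phase (92, or 52 if discovery is 20 per arm) as a sensitivity estimate only, with its confidence interval and a note that extreme responders are under-represented.

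Cost: wording in the analysis plan, some programming, and a constraint on how verification samples are drawn, to be settled before they are drawn. No extra patients are needed. The reported AUCs will tend to be lower, and those in the untouched subjects much less precise (95% half-width about 0.19 to 0.26 per arm).
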